#### Physical/functional capacity tests

Physical/Functional capacity tests will assess muscle strength at the hip and knee, calf muscular endurance, single leg movement patterning and pain-free maximum loaded knee flexion. Tests will be conducted and recorded by the study site clinicians. All assessments include testing procedures that can be applied in the clinical setting.

##### 5-RM leg press

Unilateral muscle strength will be assessed using a dynamic 5-RM test, defined as the maximal load (kg) that the participant can lift five times consecutively with the correct lifting technique. This will be performed on a leg press machine to assess multi-joint functional strength and is aligned with current clinical care practice. Multiple repetition strength assessments expose the skeletal muscles, connective tissue and joints to lower loads when compared to maximal strength testing, such as 1-RM testing, and are associated with a lower risk of injury and symptoms of delayed muscle soreness [71]. Thus, 5-RM testing is considered a more suitable assessment protocol for injured personnel in the rehabilitation setting. This test has demonstrated good test-retest reliability and can be used as a valid predictor of maximal strength (1-RM) [72, 73].

##### Isometric hip and knee strength

Isometric muscle strength will be assessed at the hip and knee in frontal and sagittal planes. This will provide an indication of muscular adaptation at the knee but also muscles proximal to the cuff [74–76]. Measurements will be taken using a wireless digital Lafayette hand-held dynamometer (HHD) (Lafayette, Indiana, United States). Hand held dynamometry is considered a valid practical method to assess muscle isometric strength [77]. The isometric ‘make-test’ was chosen as isometric loading induces less stress on the musculoskeletal system than eccentric loading (‘break-test’), which is a key consideration when testing individuals with a physical injury [78, 79]. A standardised HHD measurement technique will use procedures often applied in the clinical setting (Fig. 2). The testing positions offer sufficient mechanical advantage for the testers and has demonstrated good to excellent interrater reliability (ICC 0.82–0.98) and low test-retest variation (< 10%) when measuring isometric lower limb muscle strength [80].

**Fig. 2 Fig2:**
[figure not shown]
Testing positions and order for isometric strength assessment. **A** Hip flexors **B** Hip extensors **C** Hip adductors **D** Hip abductors **E** Knee extensors **F** Knee flexors

*Heel-raise test* The heel-raise test is used in clinical practice to assess properties of the calf muscle-tendon unit (MTU) [81, 82]. The heel-raise test involves repetitive concentric–eccentric muscle action of the plantar-flexors in a single leg stance and is quantified by the total number of raises performed. This test demonstrates good reliability and has traditionally been used to assess various calf MTU properties including muscular strength, endurance and fatigue [82–85]. It is acknowledged that the ankle plantar flexors (gastrocnemius and soleus muscles) will not be subjected to high contracting forces during the leg press and knee extension exercises and are therefore not under a comparable biological stimulus as the quadriceps muscle. However, it is important to consider the holistic impact of any new exercise rehabilitation protocol on physical metrics considered important to the population of interest. Due to the high demand placed on the ankle plantar flexors during military tasks, such as running, load carriage and multidirectional speed and agility, restoring calf capacity is a common goal during military specific rehabilitation programmes [86]. Therefore, it is of clinical interest to determine whether any muscular adaptation occurs in this functionally important muscle group.

*Decline knee bend* Knee pain is commonly reported during specific weight-bearing knee flexion tasks such as stair climbing, running, jumping [87]. The decline step-down test is a clinical performance test that replicates these movement patterns and thus assesses changes in knee pain and function that is directly relevant to these commonly reported problems [88]. The maximum flexion angle achieved at the knee joint without increasing symptomatic knee pain will be determined using video analysis ([name]). A box with a 25º decline angle will be used to prevent ankle dorsi-flexion being the limiting factor during this task (Physio Foam, UK) (Fig. 3).

**Fig. 3 Fig3:**
[figure not shown]
Decline knee bend task. **A** Start position; **B** End position

*Qualitative analysis of single leg squat (QASLS)* The qualitative analysis of single leg squat (QASLS) is a scoring system designed to identify segmental sub optimal behaviour following performance of a single leg squat [89]. This testing procedure will be video recorded and independently scored by two members of the research team ([name] and [name]). The QASLS involves dichotomous scoring of the movement strategies occurring in individual body regions. Movement analysis is subdivided into six categories-arm strategy, trunk alignment, pelvic plane, thigh motion, knee position and steady stance. Pelvic plane, thigh motion, knee position and steady stance each have two performance points. This test has demonstrated very good to excellent inter and intra-rater reliability and good criterion validity against three-dimensional (3D) motion capture [89, 90].

#### Training load

A participant monitoring booklet (Table 3) will enable daily monitoring of training load, participant wellness scores, symptomatic knee pain and localised muscle discomfort during the 3-week rehabilitation course. This will be recorded in a participant booklet that is completed daily by the participant and therapist.

**Table 3 Tab3:** Participant monitoring booklet

**Domain**	**Measure**	**Frequency**
Participant Wellness Score	Likert scale (0–5) of 5 dimensions	Once daily, AM
Training load	Sets, reps, load completed	Immediately post study intervention session
Session rate of perceived exertion (sRPE)	scale of 0 to 10	Immediately post study intervention session
Symptomatic knee pain	Visual analogue scale (VAS), 100 mm horizontal line	Immediately prior to starting the exercise, during the exercise and then 5 min post-exercise
Muscular discomfort	Visual analogue scale (VAS), 100 mm horizontal line	Immediately prior to starting the exercise, during the exercise and then 5 min post-exercise.
Symptomatic knee pain during a pain provoking functional task (single-leg knee bend)	Visual analogue scale (VAS), 100 mm horizontal line	Every third session for LL-BFR group
		Every session for HL-RT session.

#### Muscular discomfort and symptomatic knee pain

A visual analogue scale (VAS) will be used to measure pain intensity. The VAS uses a 100 mm horizontal line anchored by the terms ‘no pain’ (0) and ‘worst possible pain’ (100). The VAS response format has shown good internal consistency, is easy to understand, is in wide clinical use, and has been sufficiently evaluated in clinical trials [91]. Levels of muscular discomfort and symptomatic knee pain will be recorded immediately prior to starting the quadriceps-based exercise, during the exercise and then 5 min post-exercise. Previous studies have demonstrated a hypoalgesia response up to 45 min post BFR training [49]. Therefore, all participants will also be asked to score symptomatic knee pain during a pain provoking functional task (single-leg knee bend) immediately prior and 15 min following the cessation of exercise. These pain-related outcome measures will be repeated at the start, middle and end of each treatment week to monitor how pain response changes over time to both intervention arms. Muscular discomfort and symptomatic knee pain will be monitored during the 3-week rehabilitation admission using a participant monitoring tool (Table 3).

### Nested mechanistic study outcome measures

All mechanistic based outcome measures will be assessed at DMRC Stanford Hall 3-days prior to T1 (course admission), 3-days following T2 (course discharge) and at T3 (three-months following discharge). T2 data will be collected 5-days following the final exercise session. This is to provide sufficient recovery for maximal torque generation following resistance exercise and for the effects of exercise induced muscle swelling to subside [52, 92–95]. Outcome measures will be collected in the following order: blood sample, muscle imaging, bilateral squat, unilateral squat, countermovement jump (CMJ), isometric mid-thigh pull (IMTP), maximum isometric voluntary contraction (MVIC). Performing muscle imaging prior to neuromuscular testing ensures that exercise does not influence muscle morphology or architecture. The sequence of neuromuscular testing ensures that movements that place the greatest loading demands on the knee joint are scheduled towards the end of the testing session, reducing the probability of symptomatic pain or neuromuscular fatigue affecting subsequent task performance. Outcome data will be collected at the same time of day to minimise the effects of circadian rhythm on performance.

#### Muscle imaging

Participants will rest quietly in a supine position for 20 min prior to muscle imaging to allow for postural related fluid shifts to occur [96].

##### Anatomical cross-sectional area and volume

Anatomical cross-sectional area (ACSA) (cm^2^) and volume (cm^3^) of the involved thigh musculature will be measured using magnetic resonance imaging (MRI) with a Philips Ingenia Elition 3.0T X (Philips Healthcare, Best, The Netherlands). A T1-weighted, spin echo, axial plane sequence will be obtained with contiguous transverse images from the greater trochanter to the lateral condyle of the femur with a 1.0 cm slice thickness and no inter-slice gap. The MRI data will be anonymised and transferred onto a study laptop for analysis using a public domain image analysis software (Image J, v1. 48, National Institutes of Health, Bethesda, USA). For each slice, ACSA and volume will be calculated for each muscle within the quadriceps femoris and for the global hamstring compartment. Inter- and intra-rater reliability will be calculated from the repeated analysis of the first five MRI scans.

##### Physiological cross-sectional area

Physiological cross-sectional area (PCSA) is proposed to represent the sum of the cross-sectional areas of all muscle fibres within a given muscle and is known to be the only architectural parameter which directly relates to maximal isometric force production [39]. An in vivo estimate of VL PCSA will be calculated using Eq. 1 [39, 104].1$$\mathrm{PCSA }\left({\mathrm{cm}}^{2}\right)=\frac{\mathrm{VL\, volume }\,({\mathrm{cm}}^{3})}{{\mathrm{F}}_{L} (cm)}$$

#### Neuromuscular performance

For each neuromuscular task, participants will be asked to rate their symptomatic knee pain before, during, immediately after and 5 min following each task using a VAS. Surface electromyography (sEMG) will be used during all neuromuscular testing using a wireless sEMG system (Trigno; Delsys Inc., Boston, MA). Standard Trigno, single differential sensors (Delsys Inc., Boston, MA) with a fixed 1 cm inter-electrode distance will be attached to the superficial quadriceps (vastus medialis, rectus femoris and VL), hamstrings (long head biceps femoris and semitendinosus). Electrodes will be attached on both legs and in the presumed orientation of the underlying fibres. Electrode locations will be prepared and defined in accordance with Seniam guidelines [105]. To ensure the reliability of electrode location between time points, the distance of each electrode relative to the two anatomical landmarks used to determine electrode location (as defined by Seniam) will be recorded at T1 and replicated at T2 and T3. Electrode orientation will also be measured at T1 (using a goniometer) and replicated at T2 and T3.

##### Isometric strength testing

Where pain is the primary limiting factor to performance, isometric strength testing may eliminate painful joint movement under loaded conditions and may provide a safer alternative for the quantification of force production [106–108].

The IMTP has demonstrated good-to-excellent reliability in measuring maximal strength [109], is currently implemented as a role fitness test within the British Army Physical Employment Standards and has previously been integrated into lower-limb rehabilitation settings within UK Defence rehabilitation [108]. The IMTP is a test that can assess multiple derivatives of maximal lower-limb muscle force production capabilities, including peak force, rate of force development and limb symmetry. The IMTP will be delivered using a previously established, standardised testing procedure [107] on a pair of portable force plates (Hawkin Dynamics, Portland, Maine, United States) located on the base plate of a mid-thigh pull rig (Absolute Performance, Cardiff, UK). Force-time data will be sampled at 1,000 Hz and will be visually assessed against a previously established criteria, with invalid trials repeated [107].

Knee extension and knee flexion MVIC’s will be performed using an isokinetic dynamometer (Biodex Multi-Joint system Pro, Biodex Medical Systems Inc, Shirley, New York). The use of isokinetic dynamometry is widely considered to be the gold standard for measuring muscle torque [110]. All isokinetic dynamometry will be conducted with participants at a hip angle of 90°, with knee angles at 60° and 45° for knee extension and flexion respectively; these joint angles are known to produce maximal torque values and electromyographic amplitudes and have previously been performed safely by individuals with pain arising from the patellofemoral and tibiofemoral joints [111, 112].

##### Kinetic and kinematic analysis during functional movements

Three-dimensional motion capture and force plate data will be collected for the analysis of kinetic and kinematic variables during the bilateral squat, single leg squat and the CMJ using a 20-camera 3D system (Vicon MX system, Oxford Metrics, Oxford, England) and two AMTI force plates (Boston, USA). Data will be captured at 200 Hz and 2,000 Hz for motion capture and force plate data respectively. Forty-six retroreflective markers will be placed on the skin over anatomical landmarks by the same researcher ([name]), establishing an eight-segment model including the foot, shank, thigh, pelvis and trunk [113]. Data will be labelled in Vicon Nexus (Oxford Metrics, version 2.12, Oxford, England) before being processed in Visual 3D (C-motion, version 2022.08.3, Rochelle, USA).

The performance of bilateral and unilateral squats allows for the detailed assessment of clinically relevant kinetic and kinematic variables during functional tasks commonly used during patient clinical assessments [114]. Five trials will be performed, where participants will be asked to squat to a depth beyond 60° and return to an upright position over a 4 s metronome paced cycle. Data from the first and fifth trial will be discarded, with mean values from the middle three trials used for analysis.

The CMJ can yield valuable insight into an individual’s neuromuscular function, ballistic force production and stretch-shortening (SSC) capabilities [115]. The CMJ has been demonstrated to be a valid and reliable measure of lower-body explosive strength [116] and has strong, positive associations with occupational performance in military settings [117]. Three trials will be performed, with mean values used for analysis. No coaching on technique will be offered during any movement, as technique cueing is known to alter kinetic and kinematic variables and may therefore encourage participants to adopt movement strategies which do not represent their typical movement patterns [118]. On the contrary, self-selected movement patterns possess high correlations with the joint loading encountered during daily living and occupational tasks [114].

##### Dynamic strength index

The dynamic strength index (DSI) provides a ratio of the force that an individual can produce during isometric and ballistic tasks and is thought to provide insight into an individual’s training status by highlighting performance deficits [119]. A DSI will be calculated using peak force values from the IMTP and the propulsion phase of the CMJ and is shown in Eq. 2. These tasks have previously been demonstrated to produce reliable DSI data [120].2$$\mathrm{DSI}=\frac{\mathrm{CMJ\, Peak\, Force }(\mathrm{N})}{\mathrm{IMTP\, Peak\, Force }(N)}$$

#### Blood sampling

A 20 ml venous blood sample will be obtained from an antecubital vein to assess the chronic effects of LL-BFR and HL-RT on markers of muscle damage, inflammation, and endothelial function. Samples will be obtained at the same time of day (07:00–10:00 h), following a ≥ 12 h fast, with abstinence from alcohol (≥ 24 h), caffeine (≥ 12 h) and vigorous exercise (72 h). These measurement procedures are designed to minimise pre-analytical variability in biomarkers [121].

### Blinding

Given the nature of BFR, it is not possible to blind participants to their treatment allocation. The clinical staff who deliver the study interventions and collect outcome data for the main RCT must also be, by necessity, un-blinded. The following outcome measures will be assessor blinded: Decline knee bend, QASLS and all the outcome measures collected in the nested mechanistic study.

### Sample size

#### Main randomised control trial

A sample size of 150 participants (75 in each arm) will be recruited into the study. The study is powered to detect a minimum clinically important difference (MCID) in the Lower Extremity Functional Scale (LEFS) using a between group MCID of 9 points and an estimated standard deviation of 15.8 [61]. From this an effect size, f, of 0.285 was calculated. The expected sample size for 0.80 power to detect an effect size (f) of 0.285 at a level of significance α = 0.05 is 122 participants (61 In each group). By estimating an approximate 20% dropout rate we concluded a sample size of 150, with 75 in each intervention arm. The G Power 3.1.9.7 software was used to calculate the sample size. This sample size is also sufficient to detect a MCID of 8 points in the KOOS ADL subscale with a statistical significance of *α* = 0.05 and power of > 0.80 where the MCID is 8 points and expected standard deviation is 8.9 [122, 123].

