#### Randomisation

A permuted block randomisation method with a 1:1 ratio of the two treatment arms will be used using random block sizes. Randomisation will be stratified by study site, biological sex at birth, and diagnostic sub-group. A plain language statement will inform participants that they have an equal chance of receiving the HL-RT or LL-BFR intervention. A concealed list will be used to assign group allocation, this will be performed by an independent administrator not involved in the recruitment, treatment, or assessment of study outcomes.

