### Statistical methods and analysis

Descriptive data will be reported as the mean and standard deviation (SD) for continuous variables and frequency statistics for non-continuous variables. Prior to statistical analysis, tests to establish the normality of data distributions will be performed and, where appropriate, variance-stabilising transformations will be applied. Analysis will be conducted on a modified intention to treat basis, including all available outcomes at course discharge regardless of compliance to treatment. All tests will be two-sided, and alpha will be set at 0.05. Assumptions for all tests will be considered and adhered to. In the primary analysis, a mixed-effects regression analysis will be used to assess the effects of the interventions on primary outcome scores at course discharge (T2) between the two treatment groups, after adjusting for fixed effects of biological sex at birth and baseline (T1) primary outcome scores, with study site centre included as a random effect. The treatment effect estimates will be presented from the adjusted mixed model with 95% confidence intervals (CI) and P-values. This mixed-effects model will be used for all secondary outcome measures. Supporting analysis of the primary outcome will include: A per-protocol analysis including patients with compliance > 80% to intervention; a repeat of the primary analysis with additional adjustments for baseline values and a mixed effects model to compare primary outcomes at three-months post intervention between the two treatment groups. In addition to the primary adjusted analysis, the unadjusted mean differences between groups will be compared using t-test for independent groups, reporting 95% CI. Sub-group analysis will be conducted by diagnostic sub-group, biological sex at birth, age and pain levels at baseline. Study participant flow will be recorded and reported in accordance with the Consolidated Standard of Reporting Trials (CONSORT) guidelines. Analysis will be conducted on a pairwise case basis. Therefore, all missing data will be reported, and patterns investigated. Sensitivity analysis will be conducted using multiple imputation techniques to assess the effect of missing data on primary outcomes. Post intervention adverse events between groups using Fisher’s exact test. All analysis will be conducted using SPSS.

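### The main sample size of 122 does not follow from its stated inputs: the two-arm answer is 100, so the stated power of 0.80 is understated

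*Protocol article*

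**What the plan says.** The protocol article, under Sample size, Main randomised control trial, bases the calculation on the LEFS "using a between group MCID of 9 points and an estimated standard deviation of 15.8". It continues: "From this an effect size, f, of 0.285 was calculated". The requirement is then given in one sentence, whose two parts read "The expected sample size for 0.80 power to detect an effect size (f) of 0.285" and "at a level of significance α = 0.05 is 122 participants (61 In each group". Attrition is added next: "By estimating an approximate 20% dropout rate we concluded a sample size of 150, with 75 in each intervention arm". The section names G*Power 3.1.9.7 as the software but not the test selected in it.

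Three other statements fix the comparison:

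- Randomisation: "A permuted block randomisation method with a 1:1 ratio of the two treatment arms will be used".
- Statistical methods and analysis, on testing: "All tests will be two-sided, and alpha will be set at 0.05".
- The same section defines the primary analysis as LEFS at course discharge (T2) compared between the two treatment groups. That is one contrast, with 1 degree of freedom.

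**The concern.** The section prints every input and the result, so the result can be checked directly, and it does not follow. A requirement of 122 at 80% power is well above what a standardised difference of 0.57 needs in a two-arm comparison. The gap is too large to come from rounding or from the choice between an exact and an approximate method.

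What is at stake is the accuracy of the trial's main design statement. As written, it gives the wrong number of evaluable participants for 80% power, and it understates the power of the size it quotes. Anyone who re-runs the calculation will find the mismatch.

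**Working it through.** **Inputs.** Difference 9 points, SD 15.8, f = 0.285, alpha 0.05, power 0.80, about 20% dropout and 150 recruited (Sample size, Main randomised control trial). Two arms at 1:1 (Randomisation). Two-sided tests and a two-group comparison at T2 (Statistical methods and analysis).

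**Step 1: effect size.** d = 9/15.8 = 0.5696. For two equal groups f = d/2 = 0.2848, which rounds to the stated 0.285. This part is right.

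**Step 2: attempt to reproduce 122 for two arms.**

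- Normal approximation: n per arm = 2(1.96 + 0.8416)²/0.5696² = 48.4, so 49 per arm, 98 in total.
- Exact two-sample t: power = P(|T| > t_crit), where T is noncentral t with 2n − 2 df and noncentrality d√(n/2).

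| n per arm | Total | Noncentrality | Power for 9 points |
|---|---|---|---|
| 49 | 98 | 2.819 | 0.797 |
| 50 | 100 | 2.848 | 0.805 |
| 60 | 120 | 3.120 | 0.872 |
| 61 | 122 | 3.146 | 0.877 |
| 75 | 150 | 3.488 | 0.934 |

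- F test with 1 numerator df, noncentrality N·f² with f = 0.285: N = 98 gives 0.798 and N = 99 gives 0.802, so 99.

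The two-arm requirement is therefore 98 to 100 depending on method, or 100 with equal arms and the exact t. The stated figure exceeds it by 22, which is 22/100 = 22%.

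**Step 3: settings that might give 122.**

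- One-sided alpha 0.05: 39 per arm, 78 in total (normal approximation). No match, and the plan says two-sided.
- Two-sided alpha 0.025: 120. No match, and the plan says 0.05.
- F test with 2 numerator df, f = 0.285: N = 121 gives 0.798 and N = 122 gives 0.801. Exact match, whether 2, 3, 4 or 6 groups are entered.
- F test with 3 numerator df: 139. No match.

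**Step 4: attrition.** 150 × 0.80 = 120, and 1 − 122/150 = 18.7%. Inflating the recomputed requirement gives 100/0.80 = 125.

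**Step 5: what the planned size delivers.** With 80% power and two-sided alpha 0.05, the detectable difference is 8.08 points at 61 per arm and 8.15 points at 60 per arm.

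All these powers are for an unadjusted two-sample comparison at a single look.

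**The case against.** The strongest objection is that the error harms nothing. The trial recruits more than its inputs require (150 against 125), no design or analysis decision depends on 122, and the correction leaves recruitment alone. This stands as a limit on how serious the point is. It does not rescue the figure: the paragraph still states a sample size and a power that contradict its own inputs.

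A second objection is that the authors may have chosen a test that properly has 2 numerator degrees of freedom, such as a group-by-time term over the three assessments. That is possible, since the test is not named. It would still not be the primary comparison, which is between two groups at T2. For the same reason the 2-df explanation can only be called likely. The match does not show that three groups were entered, because the same N results for two groups.

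Three stronger readings are tempting, and the document does not support them:

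- **That the trial is under-powered because the stated power is wrong.** The error runs the other way: power for 9 points is about 0.87 to 0.88 with 120 to 122 evaluable.
- **That 150 is a second error because 20% dropout leaves 120 rather than 122.** The text says the rate is approximate, 122 out of 150 implies 18.7%, and the two-participant gap moves power only from 0.877 to 0.872.
- **That the wrong figure would distort stopping or shortfall decisions.** The protocol article has no futility rule and no shortfall rule tied to 122. Its planned looks at n = 50 and n = 100 concern superiority.

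Finally, the primary analysis is a mixed model adjusted for baseline LEFS and sex with a random site effect, not an unadjusted t test. No baseline correlation or site variance is given, so power under that model cannot be computed here. The restated figures should be labelled as unadjusted.

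**Conclusion.** The point holds as an error in a stated figure. On the plan's own inputs, 80% power for a 9-point difference needs 100 evaluable participants (50 per arm; 99 by a 1-df F test), not 122. At 122, power is about 0.88 rather than 0.80. The direction is conservative, and the planned 150 is more than adequate on these inputs.

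The conclusion rests on the stated SD of 15.8, two arms at 1:1, two-sided alpha 0.05 spent at a single look, and no covariate adjustment. A 2-df F test is the likely source of 122, but this is an inference from an exact numerical match. The dropout allowance is not a separate error.

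**What to change.** Re-run the calculation for the two-group, 1-df comparison, name the G*Power test used, and replace the paragraph with wording such as:

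> 100 evaluable participants (50 per arm) give 80% power for a 9-point difference (SD 15.8, two-sided alpha 0.05, unadjusted two-sample comparison, single look). Recruiting 150 with about 20% attrition leaves about 120, giving about 87% power for 9 points, or 80% power for about 8.2 points.

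The 8.2 is 8.15 rounded up. Keep 150. The cost is one corrected paragraph, with no change to recruitment or analysis.
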